### Sample size calculation

We calculated that, in order to be able to detect a reduction in use of EA from 25 to 17% (with an alpha 0.05 and beta 0.20), taking into account the use of multilevel analysis (10% higher sample size) and an attrition of 10% (90% complete records), a sample size of 2 × 496 participants will be necessary (*n* = 992).

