**Table 1 Tab1:**
[figure not shown]
Timeline and Data Collection. EQ. 5 D Standardized validated instrument measuring five health dimensions. STAI State-Trait Anxiety Inventory

*Control of in- and exclusion criteria (i.e. reason for removal from study: elective caesarean because of breach position).

*EQ5D* Standardized validated instrument measuring five health dimensions; *STAI* State-Trait Anxiety Inventory; *CWS* Cambridge Worry Scale; *LAS* Labor Agentry Scale; *CLIK-Q* Questionnaire to reflect on patient satisfaction (maternity empowerment/experience)

In the first week after birth (preferably the same day of the birth), the MCA will fill-out a case report form together with the midwife or doctor, based on primary and secondary outcome measures. Additionally, the woman will fill out the Labor Agentry Scale (LAS) questionnaire, which scores experience of personal control during labor. In field studies, the LAS showed an inverse relationship between anxiety and control [20].

Six weeks after birth, the participants will fill out the final questionnaire, the CLiK questionnaire, used within Dutch maternity care agencies to reflect on patient satisfaction. It is based on the validated Maternity Empowerment Questionnaire. Questions are about maternity empowerment, the EQ5D and women’s experiences with maternity care assistance. We will perform random checks of the completed case reports and we will extract data from the main source if there are inconsistencies in completed case report forms.

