### Statistical analysis

Baseline characteristics include age in years, ethnic background, gravidity and parity, gestational age at birth, mode of birth in this pregnancy, and if applicable, mode of previous birth and experience of previous birth(s). The primary outcome EA, and its association with continuous care versus care-as-usual, will be analyzed using multilevel logistic regression analysis.

The secondary outcomes are listed in Table 2, and will be addressed using multilevel linear regression analyses (for continuous variables), multilevel logistic regression (for binary variable variables) or multilevel multinomial logistic regression analysis (for categorical outcomes with more than two categories). If important baseline characteristics will differ greatly between the study arms, we will include them in the analysis. Missing data will be imputed by use of stochastic regression imputation, with predictive mean matching as the imputation model. We will perform both an intention to treat analysis and per protocol analysis. Cost-effectiveness will be calculated for the six-week period following childbirth and incremental cost effectiveness ratios will be calculated in QALY per prevented EA based on utility index from the EQ5D and usage of healthcare. Standardized sensitivity analysis will be carried out to quantify the outcome. A budget impact analysis will be performed using ISPOR guidelines, which take into account the financial consequences of the implementation of maternity care assistants as providers of continuous support during labor.

**Table 2 Tab2:** Secondary Outcome Measures

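### The named imputation method is ordinarily single imputation, with no pooling stated: if outcomes are imputed once, standard errors are too small or the effect is diluted, depending on whether arm is in the imputation model

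*Protocol article*

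**What the plan says.** The Statistical analysis section of the protocol article deals with missing data in one sentence: "Missing data will be imputed by use of stochastic regression imputation, with predictive mean matching as the imputation model". It does not limit this to particular variables. It does not list the predictors in the imputation model, and it gives no number of completed data sets and no rule for combining results. The primary outcome, use of epidural analgesia (EA), "will be analyzed using multilevel logistic regression analysis".

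The Sample size calculation section sets the error rates ("with an alpha 0.05 and beta 0.20") and allows for "an attrition of 10% (90% complete records"). This allowance is for whole records; the article gives no expected share of missing values for EA or for any questionnaire.

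Under Data collection (text below Table 1), outcomes are entered on a case report form in the first week after birth, and the CLiK questionnaire, which includes the EQ-5D, is completed at six weeks. Forms are checked at random, and "we will extract data from the main source if there are inconsistencies in completed case report forms". Blank items are not mentioned.

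**The concern.** Stochastic regression imputation replaces each missing value by a prediction plus a random element. Predictive mean matching changes how that value is drawn, not how many completed data sets result. A standard model fitted to one completed data set counts imputed values as real observations, so its standard errors leave out the uncertainty due to imputation. Confidence intervals are then too narrow and a nominal 5% test rejects too often.

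The sentence covers all missing data. It could therefore affect EA, the Labor Agentry Scale, and the six-week EQ-5D and satisfaction scores on which the cost-effectiveness and satisfaction conclusions rest.

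**Working it through.** **Inputs.** From Sample size calculation: EA 25% against 17%, alpha 0.05, power 0.80, 10% inflation for multilevel analysis, 10% attrition, 496 per arm. From Statistical analysis: the imputation sentence. Assumed: values missing completely at random, weak predictors, no clustering, and the missing shares other than 10%.

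**The plan's own figure.** The two-sided two-proportion formula with pooled variance and no continuity correction is

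n = [1.96·√(2·0.21·0.79) + 0.8416·√(0.25·0.75 + 0.17·0.83)]² / 0.08² = 406 per arm after rounding up.

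Then 406 × 1.10 / 0.90 = 496.2, against "a sample size of 2 × 496 participants will be necessary". The figure is reproduced, so the stated alpha is two-sided and the 10% attrition is already in N.

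**Single imputation with arm in the model.** Let m be the share missing in each arm, n the arm size and σ² the outcome variance. The completed-data mean is the observed mean plus noise from the imputed draws:

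- true variance = σ²/[n(1−m)] + mσ²/n
- reported variance = σ²/n
- ratio R = 1/(1−m) + m
- actual alpha = 2[1 − Φ(1.96/√R)]

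For m = 0.10: R = 1/0.90 + 0.10 = 1.211, √R = 1.10 and alpha = 2[1 − Φ(1.781)] = 7.5%. The reported standard error is 1/1.10 = 0.91 of the true one, about 9% too small.

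A simulation checked the formula: 496 per arm, EA 25% in both arms, simple two-proportion test, 100,000 replicates.

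| Missing | R | Reported SE / true SE | Alpha, formula | Alpha, simulation |
|---|---|---|---|---|
| 2% | 1.040 | 0.98 | 5.5% | 5.6% |
| 5% | 1.103 | 0.95 | 6.2% | 6.4% |
| 10% | 1.211 | 0.91 | 7.5% | 7.5% |
| 20% | 1.450 | 0.83 | 10.4% | 10.3% |
| 30% | 1.729 | 0.76 | 13.6% | 13.7% |

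**Single imputation with arm omitted.** With no true difference, R = (1−m) + m = 1. Simulated alpha was 4.9% to 5.1% for 2% to 30% missing. The harm is then bias: imputed values carry no arm difference, so the expected difference is (1−m) times the true one. At m = 0.10 this is 0.9 × 8 = 7.2 points.

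**Multiple imputation.** Twenty imputations with arm in the model, parameters redrawn each time and results pooled by Rubin's rules, gave simulated alpha of 5.2%, 5.1% and 5.3% at 5%, 10% and 20% missing (496 per arm, 20,000 replicates).

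**The case against.** A reader might infer that the protocol commits to a single imputation and that the trial's type I error therefore exceeds 5%. The article does not say this. Predictive mean matching is also a common drawing step within multiple imputation, and a condensed article may leave the number of imputations and the pooling rule to a fuller document. This stands to the extent that single imputation is the usual meaning of the named method, not a stated fact. It does not remove the point: the article fixes a named method, and a plan that follows it literally inherits the weakness.

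A reader might also apply 7.5% directly to the primary outcome. The 10% is an allowance for incomplete records, not a forecast of missing EA. EA goes on a form completed with the midwife or doctor within a week of birth, so the loss may be smaller; at 2% to 5% missing, alpha is 5.5% to 6.2%. This objection stands. Likewise, nothing in the article shows that the six-week questionnaires will lose more than 10%; the 20% is an assumption.

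The excess error also needs arm in the imputation model, and the article does not list that model's variables. That is correct, but leaving arm out replaces false precision with dilution.

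Finally, inflating N for incomplete records could mean that records without outcomes are dropped and only covariates or questionnaire items imputed. The text allows that reading, but its sentence on missing data is unrestricted.

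**Conclusion.** The point holds in conditional form. The article specifies a method that is ordinarily single imputation and provides no step that carries imputation uncertainty into the analysis. Applied once to outcomes, it has one of two costs: excess type I error if arm is in the model, or attenuation of the treatment effect if it is not. The sizes are those in the table and the 7.2-point figure.

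They depend on the share of the analysed outcome that is actually missing and on the three simplifying assumptions. Strong predictors of the missing values would reduce the inflation. For EA the effect could be small if the forms are nearly complete. The weight is moderate: the wording should be corrected before analysis, but the documents do not show that the primary test will miss its nominal level by any particular amount.

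**What to change.** Replace the sentence on missing data with multiple imputation: predictive mean matching for scores and logistic models for binary items. The imputation model should include arm, parity, agency and the baseline questionnaire scores (EQ-5D, STAI, Cambridge Worry Scale), and results should be pooled by Rubin's rules. Extend the extraction from the main source, under Data collection, to EA items that are missing as well as those that are inconsistent, so that the primary outcome needs little imputation.

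The sample size stays at 992, since it already allows for 10% attrition. The cost is slightly wider confidence intervals, some extra analysis work and retrieval of the missing EA items.

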### Intervention

If a woman has been randomly assigned to continuous care, she (or her partner) will call the MCA for support at the onset of labor. Since this can be a subjective interpretation, we define the onset of labor as the moment the midwife or doctor confirms that labor has started. In the case of induction of labor, we decided that the MCA will be called for continuous support at the point in time when the membranes are artificially ruptured. On average, the MCA needs approximately 45 min to get to the destination. The MCA will provide care that is tailored to the needs of the woman in labor, such as helping with relaxation, offering massage or breathing exercises, or being present and giving verbal reinforcement. The duration of CC is defined as the moment the MCA arrives until the start of active pushing in the second stage of labor.

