**Health care use**	
Transfer of care from midwifery-led to obstetric-led care	
Duration of	
- continuous care	
- home care	
- hospital care	
- Neonatal Intensive Care Unit	
- Intensive Care	

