**Questionnaires**	
EQ 5D^a^State-Trait Anxiety Inventory (STAI)	
Cambridge Worry Scale (CWS)	
Labor Agentry Scale (LAS)	
CLIK-Q^b^	

^a^ Standardized validated instrument measuring five health dimensions

^b^ Questionnaires to reflect on patient satisfaction (maternity empowerment and experience)

One hour of care provided by an MCA costs approximately 45 euros, and we expect extra costs of approximately 225 euros per woman for the provision of continuous care. The costs for one EA, when taking complications into consideration, is approximately 2200 euros. We would therefore expect the use of continuous care to be cost effective with just a 10% reduction in EA use.

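### As worded, the cost-effectiveness period opens at childbirth, after continuous care and the epidural have taken place, in conflict with the costs the protocol says it will weigh

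*Protocol article*

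**What the plan says.** The only sentence that sets a period for the economic evaluation is in Methods, Statistical analysis: "Cost-effectiveness will be calculated for the six-week period following childbirth". It goes on to say that the ratios will be "calculated in QALY per prevented EA based on utility index from the EQ5D and usage of healthcare".

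The Intervention section places the intervention in time: "The duration of CC is defined as the moment the MCA arrives until the start of active pushing in the second stage of labor".

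Other parts of the article treat labor-time care as a cost to be weighed:

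- Table 2, under health care use, lists the duration of "continuous care" as an item, along with transfer to obstetric-led care.
- The text after Table 2 prices an MCA hour at about 45 euros and adds "we expect extra costs of approximately 225 euros per woman for the provision of continuous care". It continues "The costs for one EA, when taking complications into consideration, is approximately 2200 euros" and concludes "We would therefore expect the use of continuous care to be cost effective with just a 10% reduction in EA use".
- The Background states the economic hypothesis in the same terms: savings from less EA are expected to exceed the added cost of the care.

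**The concern.** A period that begins at birth begins after the intervention is over. Every MCA hour lies before it, and so do the epidural procedure and any transfer during labor. What remains inside is downstream use, such as hospital stay of mother and newborn.

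Two analysts could therefore both follow the article and reach different answers. One applies the stated period and counts no MCA cost. The other follows the Background, Table 2 and the text after it, and counts MCA cost in full. At the effect the trial is designed to detect, one obtains zero or a saving and the other a net cost. Cost-effectiveness is part of the stated aim, and the article predicts a favourable result, so the start of the period should be settled before the data are analysed.

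**Working it through.** **Inputs.** MCA care: 45 euros per hour, 225 euros per woman. One EA including complications: 2200 euros (all from the text after Table 2). Planned effect: EA use falls from 25% to 17%, so r = 0.08 (Sample size calculation). Let f be the share of the 2200 euros incurred before birth. The article does not give f, so it is an assumption, ranged from 0 to 1; the share after birth is 1 - f.

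**The plan's own figure.** 225 / 45 = 5 hours of care per woman. Break-even reduction: 225 / 2200 = 0.102, or 10.2 percentage points. This reproduces the stated 10% when that is read as an absolute reduction. It is a calculation that counts labor-time costs on both sides.

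**Incremental cost per woman, continuous care minus usual care.**

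- Labor counted: 225 - 2200 × r
- Literal post-birth window: -2200 × r × (1 - f)
- Shift toward continuous care (first minus second): 225 - 2200 × r × f

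**At the planned effect, r = 0.08.** The EA saving is 0.08 × 2200 = 176 euros, and the result with labor counted is 225 - 176 = +49 euros.

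| f (pre-birth share) | Labor counted | Literal window | Shift toward continuous care |
|---|---|---|---|
| 0 | +49 | -176 | 225 |
| 0.25 | +49 | -132 | 181 |
| 0.5 | +49 | -88 | 137 |
| 0.75 | +49 | -44 | 93 |
| 1 | +49 | 0 | 49 |

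For any reduction below 10.2 points, counting labor gives a net cost, while the literal window gives zero or a saving whatever f is.

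**When the direction reverses.** The shift is negative when r × f exceeds 225 / 2200, i.e. 10.2 points.

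- r = 0.12, f = 1: 225 - 2200 × 0.12 × 1 = 225 - 264 = -39 euros.
- r = 0.15, f = 0.75: 225 - 2200 × 0.15 × 0.75 = 225 - 247.5 = -22.5 euros.

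In these cases the literal window understates a saving that continuous care really makes.

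**The case against.** The strongest reply is that six weeks only names the end of follow-up, chosen to match the six-week EQ5D, and that the sentence is loosely worded. There is good support for this. The calculation rests on health care use, and Table 2 puts continuous-care hours under that heading. MCA care is priced. The ratio is expressed per prevented EA, which is itself an event in labor, so a strict post-birth reading would remove its own denominator. A reader might infer that the sponsor plans to leave out the cost of the intervention; no part of the article says so, and these passages point the other way. The reply does not remove the conflict, however. A list of items and an expected cost do not set an analysis period, and the one sentence that does sets the wrong start.

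A reader might also infer that the window can only favour continuous care. That does not follow. The same window drops the pre-birth part of the EA cost, which is a saving credited to continuous care, and the reversal shown above is possible.

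Nor does the problem carry over to the budget impact analysis. The Statistical analysis section describes that analysis as covering the cost of introducing MCAs as labor support.

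Two further limits stand. The planned ratio, taken as written, has no euro term, so the figures here describe the cost side and not the published ratio. And the largest shift, 225 euros, needs no EA cost at all before birth, which is hard to reconcile with a procedure performed in labor.

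**Conclusion.** The point holds as an inconsistency with a material consequence if the sentence is followed as written. The stated period starts after the intervention and the epidural, while the Background, Table 2 and the text after it require labor-time costs. At the planned 8-point effect the literal window changes a net cost of 49 euros per woman into a result between a saving of 176 euros and zero, a shift of 49 to 225 euros toward continuous care. This rests on the article's approximate unit costs and on an unknown pre-birth share of the EA cost. The direction depends on the observed effect and that share, and it reverses when their product exceeds 10.2 points.

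Cost-effectiveness is one of seven listed secondary outcomes. The primary analysis and the sample size are unaffected, so this should be corrected before the economic analysis but is not critical to the main result.

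**What to change.** Replace the period in the Statistical analysis section with one sentence: costs run from confirmed onset of labor, or from the start of induction, to six weeks after birth, counting MCA hours in the continuous care arm and EA, transfer and delivery costs in both arms. Add that QALYs are based on the baseline and six-week EQ5D, the two measurements that the text describes.

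The cost is a change of wording. EA is the primary outcome, and Table 2 already lists continuous-care duration, transfer and mode of delivery, so no new labor data are needed. Starting costs at randomization, or costing MCA time from call-out, is not asked for: the article lists neither antenatal resource use nor call-out times among the data collected.

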**Methods:**

A randomized controlled trial (RCT) will be performed comparing continuous care (CC) with care-as-usual (CAU). All women intending to have a vaginal birth, who have an understanding of the Dutch language and are > 18 years of age, will be eligible for inclusion. The intervention consists of the provision of continuous care by a trained MCA from the moment the supervising maternity caregiver establishes that labor has started. The primary outcome will be use of epidural analgesia (EA). Our secondary outcomes will be referrals from primary care to secondary care, caesarean delivery, instrumental delivery, adverse outcomes associated with epidural (fever, augmentation of labor, prolonged labor, postpartum hemorrhage, duration of postpartum stay in hospital for mother and/or newborn), women’s satisfaction with the birth experience, cost-effectiveness, and a budget impact analysis. Cost effectiveness will be calculated by QALY per prevented EA based on the utility index from the EQ-5D and the usage of healthcare services. A standardized sensitivity analysis will be carried out to quantify the outcome in addition to a budget impact analysis. In order to show a reduction from 25 to 17% in the primary outcome (alpha 0.05 and bèta 0.20), taking into account an extra 10% sample size for multi-level analysis and an attrition rate of 10%, 2 × 496 women will be needed (*n* = 992).

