**Discussion:**

We expect that adding MCAs to the routine maternity care team will result in a decrease in the use of epidural analgesia and subsequent costs *without* a reduction in patient satisfaction. It will therefore be a cost-effective intervention.

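### The planned incremental cost-effectiveness ratio, QALY per prevented EA, divides one effect by another and as worded contains no cost

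*Protocol article*

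**What the plan says.** The Statistical analysis section of the protocol article defines the economic ratio in one sentence: "incremental cost effectiveness ratios will be calculated in QALY per prevented EA", with the EQ-5D utility index and healthcare use named as the inputs. The Methods paragraph of the abstract gives the same unit: "Cost effectiveness will be calculated by QALY per prevented EA based on the utility index from the EQ-5D and the usage of healthcare services". The time frame is also fixed: "Cost-effectiveness will be calculated for the six-week period following childbirth".

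Nowhere does the article define a cost per QALY or a cost per EA prevented. It plans one further economic analysis: "A budget impact analysis will be performed using ISPOR guidelines, which take into account the financial consequences".

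Cost-effectiveness is the fifth of seven items in the list of secondary outcomes (Study outcomes). The text after Table 2 gives the unit costs: "One hour of care provided by an MCA costs approximately 45 euros", about 225 euros extra per woman, and about 2200 euros per EA including its complications. It expects the intervention to pay its way at a 10% reduction in EA use. The Discussion paragraph of the abstract anticipates the conclusion: "It will therefore be a cost-effective intervention".

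**The concern.** An incremental cost-effectiveness ratio is a difference in cost divided by a difference in effect. The ratio as defined puts an effect in the numerator (QALYs) and another effect in the denominator (EAs prevented). Its unit leaves no room for euros, even though healthcare use is listed as an input. One consequence is that the ratio has no favourable direction: for a given QALY gain, preventing more EAs makes it smaller.

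The economic hypothesis is about money. The Background predicts that savings from fewer EAs will exceed the extra spending on MCAs, and the text after Table 2 argues in the same terms. A ratio without cost can neither support nor refute that prediction. The wording also leaves open whether cost per QALY, cost per EA prevented, or both is intended, and that choice should not wait until the data have been seen.

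**Working it through.** **Inputs from the protocol article**
- Extra cost of continuous care: 225 euros per woman (text after Table 2). At 45 euros an hour this is 225 / 45 = 5 hours.
- Cost of one EA with complications: 2200 euros (same place).
- EA use: 25% under usual care, 17% targeted, a difference of 0.08 (Sample size calculation).
- Horizon: six weeks, or 6/52 = 0.115 year (Statistical analysis).

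**Step 1. Reproduce the article's break-even.** Saving equals spending when the reduction is 225 / 2200 = 0.102, or 10.2 percentage points. This matches the stated 10% if it is read as an absolute reduction.

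**Step 2. Put cost in the numerator, at the effect the trial is powered for.**
- Saving per woman: 0.08 x 2200 = 176 euros.
- Net cost per woman: 225 - 176 = 49 euros.
- Net cost per EA prevented: 49 / 0.08 = 612.5, about 613 euros.
- Cross-check: 225 / 0.08 - 2200 = 2812.5 - 2200 = 612.5.

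The targeted 8 points fall short of the 10.2 points needed to break even. A trial that met its target exactly would therefore show a small net cost on these inputs, and whether that is worth paying could be judged only with a ratio that contains cost.

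**Step 3. Evaluate the ratio as written.** It is (QALY difference) / (EA risk difference). The price of the MCA appears in neither term, so the result is the same at any price. This follows from the definition and needs no assumption.

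A numerical illustration does need a utility gain, which the article does not give. Assume mean gains of 0.01, 0.02 or 0.05 held for six weeks, with net cost at 49 euros per woman:

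| Assumed utility gain | QALY difference (gain x 6/52) | Ratio as written (divided by 0.08) | Cost per QALY (49 / QALY difference) |
|---|---|---|---|
| 0.01 | 0.0012 | 0.014 | about 42,500 euros |
| 0.02 | 0.0023 | 0.029 | about 21,200 euros |
| 0.05 | 0.0058 | 0.072 | about 8,500 euros |

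Now hold the gain at 0.02 and vary the MCA cost per woman. Only 225 euros is the article's figure; 0 and 2250 are hypothetical extremes.

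| MCA cost per woman | Ratio as written | Net cost per EA prevented |
|---|---|---|
| 0 euros | 0.029 | (0 - 176) / 0.08 = -2200 euros |
| 225 euros | 0.029 | (225 - 176) / 0.08 = 613 euros |
| 2250 euros | 0.029 | (2250 - 176) / 0.08 = 25,925 euros |

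The ratio as written does not distinguish a cost-saving intervention from a very expensive one.

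**The case against.** The strongest reply is that this is compressed or faulty wording and not a plan to leave out costs. The quantity is called an incremental cost-effectiveness ratio, in the plural, and is based partly on healthcare use, which has no role in a pure QALY-by-EA quotient. Table 2 lists the resource items to be collected (durations of continuous, home, hospital and intensive care), unit costs are given, and a budget impact analysis will report the financial side. Much of this stands. Costs were probably meant to enter, and the planned data allow proper ratios to be calculated.

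It does not remove the point. The same unit appears in both places where the ratio is defined, so a single slip is unlikely, and no correct definition appears elsewhere to override it. A budget impact analysis describes affordability; it does not give cost per unit of effect. Nor is this a detail that an article may leave to a fuller plan, because the article makes a positive statement and the statement is wrong.

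A reader might go further and infer that the trial cannot show whether continuous care is worth its cost, or that costs will go unreported. The documents do not support that: EA use, EQ-5D and healthcare use are all planned, and the budget impact analysis will show costs.

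It is also fair to say that the cost-per-QALY range and the alternative MCA prices are assumed. They illustrate the definition and do not measure harm to the trial. How uncertainty is presented, and which willingness to pay applies, may properly be left to the full plan, and nothing is asked on either here.

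**Conclusion.** The point holds as an error of definition. As worded, the ratio omits cost and cannot test the article's own economic hypothesis. Its practical weight comes from the net cost of 49 euros per woman at the targeted effect, which puts the planned scenario close to break-even but on the wrong side of it.

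Those figures rest on the article's approximate unit costs, and on each prevented EA saving the full 2200 euros. They are not a forecast of the trial's result. That the ratio does not respond to cost rests on no assumption.

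The definition should be fixed, but the trial does not hinge on it. Cost-effectiveness is a secondary outcome, and the primary outcome and the sample size are untouched.

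**What to change.** In the Methods paragraph of the abstract and in the Statistical analysis section, replace QALY per prevented EA with: incremental cost per EA prevented (cost difference / EA risk difference) and incremental cost per QALY gained (cost difference / QALY difference), each over the six weeks after childbirth, using the EQ-5D and healthcare-use data already planned.

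The change is to wording in two places. It needs no additional participants, measurements or procedures. It should be made before outcome data are examined, so that the choice of ratio is not open to the results.
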